### Entomological data collection and evaluation

Monitoring of mosquitoes began in September 2012 and continued until November 2015 (see Figs. 1 and 2). Sampling of mosquitoes at houses was performed using Mosquito Magnet-X® traps (American Biophysics Corporation, North Kingstown, RI, USA), baited with the same blend of five chemicals that are used for the intervention [10] and carbon dioxide produced by yeast and molasses fermentation [36]. For each round of sampling, 80 households were randomly selected with replacement from the active database maintained by the HDSS. In common with data collection in other arms of the project, random selection of households for entomological monitoring enabled measurement of entomological outcomes across the island throughout the duration of the SWCRT. Working four nights a week, ten houses were sampled every night with traps set at dusk (between 17:00 h and 18:00 h) and collected after dawn (between 07:00 h and 08:00 h). Each house was sampled once inside the house and once outside, with the inside/outside order randomised. The complete round of sampling took 4 weeks to complete, following which there was a 2-week period without sampling to make preparations for the next round. When a house had already been installed with a SMoTS, the Suna trap was disconnected during the two nights when the MM-X trap was used instead.

After collection of traps, mosquitoes were knocked down using a –20 °C freezer and identified to species group on the basis of morphology [37]. Specimens were separated and pooled by collection date, house of collection and inside/outside location, morphological species ID, sex and abdominal status. Pooled mosquitoes were stored in 80 % ethanol for subsequent molecular analyses: PCR for identification of *An. gambiae* s.l. complex and *An. funestus* s.l. complex [38, 39] and HRM-PCR for detection of *Plasmodium* DNA and blood meal analysis [35].

### Household and environmental data

Information was collected on variables that could have a direct or indirect effect on the association between the intervention and malaria infection or entomological outcomes. Every third health and demographic surveillance round incorporated a digital questionnaire for the collection of information about houses and households. Information about the construction materials used to build each house and the number of rooms was recorded, as well as the presence/absence of eaves and whether there were preventative measures taken against mosquitoes, such as LLINs and IRS and eave screening. Indicators of socio-economic status were also included in these update rounds, as was information on land and house ownership, house occupation and highest level of education of the head of household. Additionally, high-resolution satellite images were obtained to provide data on possible confounding environmental variables including the normalized difference vegetation index and a water accumulation index, also known as a topographic wetness index (TWI).

### Social sciences

A mixture of quantitative and qualitative approaches to social science data collection was used. Prior to the commencement of the intervention rollout, a structured questionnaire was completed with one adult male and one adult female in each of 204 randomly selected households (5 % of all households). The questionnaire was repeated with a new random selection of 5 % of households after completion of the rollout.

In addition to the structured questionnaires, listening surveys were conducted during each community training workshop to record trends in questions asked by community members over the course of the rollout. Listening surveys were performed during the installation of SMoTS in order to gauge initial reactions to the intervention. Data were also collected informally (i.e. observations, listening surveys, field notes) during other project community events such as an event held to launch the project on the island and the rollout ballot, among others. Throughout the course of the study, focus group discussions with specific stakeholders not only provided a useful tool for gathering information on community knowledge, attitudes and perceptions, but also helped the project to build links with the community.

Throughout the duration of the study, community members were able to contact a project community liaison officer and the solar technicians by phone in order to report technical faults in the SMoTS. A detailed record of phone calls was maintained by an on-site project manager, and these records were used to schedule maintenance activities as well as to understand how well the systems were performing over time. Intermittent spot checks were carried out one evening per week in 20 randomly selected households from a single metacluster to allow the field staff to monitor the performance of systems during the hours of darkness.

During the final phase of the project (December 2014–December 2015), interviews with key stakeholders and focus group discussions were used to develop and finalise a sustainability plan for the maintenance of SMoTS beyond 2015.

### Data entry and management

The collection and management of data was fully digitised, with all data entered by means of a tablet computer. The data collection was managed by the researchers, who operated independently from the project sponsor. Open Data Kit (ODK) [40] was used to build and conduct questionnaires, and data were uploaded daily to a secure local server. Demographic data were stored and then transferred to OpenHDS, a data management platform [34, 41]. New information was automatically incorporated into the demographic core database. This data management platform allowed for data cleaning immediately after upload to the server. To prevent duplication of ID codes in the system, the OpenHDS software generated a new unique ID for each individual, house and household as required. There were several built-in methods to prevent errors in data entry. Mostly, answers needed to be logical and were listed as multiple choice in the electronic questionnaires. For instance, a male cannot be recorded as having a pregnancy, and the age of a newborn cannot be more than one year.

A progress and quality monitoring plug-in for OpenHDS, SU2, used to ensure quality post hoc, was deployed in 2013 [42]. The programme, which automatically ran every night, provided the data manager with a report on operational statistics and inconsistencies in data collected the previous day. The SU2 software tracks which individuals and houses are visited on a daily basis and produces an up-to-date geodatabase of locations to visit for uploading to the tablet computer. Maps based on this information guided fieldworkers in navigating through their assigned area and recognising which houses and individuals still needed to be visited during a round of surveillance. The final trial database is stored at Wageningen University and Research Centre and is available to the entire research team.

### Power and sample size rationale

There is some controversy about power calculations for SWCRTs [43], and the power of our design depended on the correlation between observations on the same individuals at sequential HDSS visits. We could not determine the level of correlation from the single baseline enumeration visit. A lower bound for the minimum detectable effect size is therefore that of a single visit per person, occurring halfway through the rollout. Using previously published formulae, this approach was anticipated to have had 80 % power to detect approximately 52 % reduction in clinical incidence with an effective sample size of 7914 persons [44]. Analogous calculations for prevalence [44], using a baseline malaria prevalence of 23.7 % (RDT prevalence rate during the baseline survey for this project) and minimum sample size of 907 persons, suggested that a single prevalence survey should have had 80 % power to detect a 27 % reduction in prevalence. Six repeated surveys might have the power to detect effects as small as an 11 % reduction in prevalence, assuming that correlations between repeated observations were small.

### Analytical plan

The datasets included for the analysis comprise results of the HDSS, clinical malaria surveys, cross-sectional malaria prevalence surveys and monitoring of mosquito densities. Malaria fever incidence is the primary outcome of the trial. Data are included up to the end of the next month after full intervention coverage was attained. For analyses of parasitological as well as entomological outcomes, intervention status is classified week by week on the basis of whether traps had been installed in the cluster. The whole study cluster is classified as intervened or non-intervened based on whether installation was complete in that cluster by the end of the week. Clusters are excluded from analysis during weeks in which some, but not all, of the households were provided with the intervention (i.e. during the week in which installations took place in that cluster). For malaria prevalence and incidence, the numbers and proportions of positive RDT tests were summarised by week and arm of the trial. For mosquito densities, rates of anophelines collected per trapping night were presented by week and arm of the trial.

Following the SWCRT design described by Silkey et al. [33], an analytical plan was constructed. The primary analysis of the impact of the trial on clinical malaria incidence, prevalence and vector densities follows two measures of effect: a contemporaneous comparison comparing the outcomes in intervened clusters with the not yet intervened clusters and a comparison of the final results in intervened areas with the baseline status. Generalized linear mixed models (GLMMs) with a binomial distribution will be deployed to carry out significance testing against the null hypothesis of no effect using a likelihood ratio test. For mosquito densities a GLMM will be used with a Poisson distribution. For analysis of medical and entomological data, random effects will be used to allow for spatial effects (cluster) as well as effects of round of surveillance (time period within cluster). Final models will consider possible confounding effects on the relationship between the intervention effect and measured outcomes. The analytical plan did not include any interim analyses.

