### Study objectives

#### Primary objective

The primary objective is to measure the effect of mass mosquito trapping on clinical malaria incidence, measured as fever plus positive rapid diagnostic test (RDT) result.

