#### Secondary objectives

The medical objectives are as follows (all outcome measures include contemporaneous comparison of intervened with non-intervened areas, as well as before-and-after measures of intervened areas compared with baseline):To determine the impact of mass mosquito trapping on malaria prevalence measured by RDT, with subsequent high-resolution melting PCR used to estimate the prevalence of sub-patent malariaTo calculate differences in both measured and reported all-cause fevers following the introduction of odour-baited traps

The entomological objectives are as follows (all outcome measures include contemporaneous comparison of intervened with non-intervened areas, as well as before-and-after measures of intervened areas compared with baseline):To assess whether the mass trapping of mosquitoes reduces the population density of malaria vectors on Rusinga IslandTo determine whether the mass distribution of odour-baited mosquito traps leads to changes in mosquito species compositionTo record changes in entomological inoculation rate associated with implementation of the interventionTo compare mosquito densities and species composition indoors and outdoors

The sociological objectives are as follows:To determine the behavioural, socio-cultural and organisational factors that influence the effective and sustainable use of SMoTSTo foster learning relevant to adapting the implementation and sustainability strategy as an integral component of the interventionTo understand how the introduction and use of SMoTS affects and/or is affected by the use of other malaria control interventions

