### Measurement of malaria incidence and prevalence

Clinical malaria incidence was recorded during the routine HDSS surveillance of all individuals (three rounds of surveillance each year, see Figs. 1 and 2). During household visits residents were asked to report any fever in the previous 2 weeks, 2 days and at the time of the visit. If fever was reported to have occurred within 2 weeks of the visit, body temperature was measured using an in-ear thermometer (Braun™ IRT 3020). If the measured in-ear temperature was greater than 37.4 °C, the individual was tested for malaria using an RDT (*SD BIOLINE*™ Malaria Ag P.f/Pan *HRP*-*II*/pLDH). Any person with a positive RDT was provided with an appropriate dose of artemether-lumefantrine or referred to a local health clinic in the case of pregnancy, child under 6 months of age or severe symptoms. By collecting clinical malaria data continuously, information was available for baseline and throughout the course of the rollout for all 81 of the clusters.

In addition to the detection of malaria-associated fever within the HDSS, cross-sectional malaria prevalence surveys were carried out in a randomly selected 10 % of the study population three times per year (Figs. 1 and 2). All selected individuals were tested for malaria using an RDT, and a dry blood spot was also collected from each person as well as a measure of in-ear temperature. Validation of RDTs was performed using high-resolution melting PCR (HRM-PCR) [35] on a random sample of 200 dry blood spots from each round of surveillance. As for the HDSS and clinical malaria monitoring process, this data collection method allowed for measurement of malaria prevalence in all 81 clusters of the SWCRT at regular intervals throughout the course of the project.

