In addition to the anticipated impact on malaria, members of the study population were expected to immediately benefit through the electrical lighting and mobile phone charging facilities provided with the SMoTS. Electrical lighting is expected to reduce a reliance on kerosene that is typically used to light houses in this region. As the fumes emitted by burning kerosene are known to negatively affect the respiratory system [45], replacement of kerosene lamps by electric lights is likely to remove this health hazard. As well as removing health risks attributed to inhalation of kerosene fumes, the risk of fire and burns [46] is also reduced by providing electric indoor lighting. With a reduced daily expenditure on kerosene and mobile phone charging, the intervention should lead to financial savings and could lead to improved socio-economic status, which in turn may lead to other health improvements.

In order to ensure that risks to the population were minimised, the continued use of LLINs by all age groups was recommended at all community meetings and training sessions. Participation in the intervention did not affect the use of existing health facilities. The creation of a CAB facilitated regular exchanges of information between scientists, project field staff and the Rusinga Island community, and it is expected that some members of this board will remain actively involved in the maintenance of the SMoTS beyond the follow-up period of the study. By the completion of the rollout in mid-2015, the community were beginning to form groups to save money for the purpose of maintaining SMoTS beyond the research period. The provision of electrical lighting and mobile phone charging provides an incentive for users to keep the systems running, and links with Kenyan solar-home system providers are being made to ensure continuous provision of replacement components at prices which are affordable for low-income households. By working closely with the Kenyan Ministries of Health and Energy, the SolarMal project has formed a strong basis for continuing and expanding the use of SMoTS on Rusinga Island and elsewhere in the region. If the intervention is proven to be an effective tool for malaria control, researchers will work together with industry and policy makers to develop cost-effective, long-lasting and readily available malaria mosquito trapping systems for use in at-risk areas.

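### For the primary outcome, the only proportion the plan states is RDT positivity among measured fevers, which does not match the incidence objective or the per-person power basis

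*Protocol article*

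**What the plan says.** All references are to the protocol article.

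- **Primary objective:** the outcome is "clinical malaria incidence, measured as fever plus positive rapid diagnostic test (RDT) result". The Analytical plan repeats that "Malaria fever incidence is the primary outcome of the trial".
- **Measurement of malaria incidence and prevalence:** "Clinical malaria incidence was recorded during the routine HDSS surveillance of all individuals". Residents are asked about fever in the previous two weeks. Those who report it have their temperature taken, and only if it exceeds 37.4 °C is it the case that "the individual was tested for malaria using an RDT". In the separate prevalence surveys, everyone in the 10 % sample is tested.
- **Analytical plan:** "For malaria prevalence and incidence, the numbers and proportions of positive RDT tests were summarised by week and arm of the trial". The next paragraph names a binomial generalized linear mixed model with a likelihood ratio test. It states neither the denominator nor the link.
- **Power and sample size rationale:** the calculation assumes one visit per person and gives 80 % power for about a 52 % "reduction in clinical incidence with an effective sample size of 7914 persons".
- **Secondary objectives:** the trial will also study "differences in both measured and reported all-cause fevers following the introduction of odour-baited traps".

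**The concern.** One summary, positives out of tests, is applied to two outcomes whose tests are taken in different people. In the prevalence survey, tests and persons coincide. In the HDSS, tests are a subset selected by fever, so the proportion answers a different question: of those found febrile, how many have malaria?

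That quantity can move when malaria incidence does not, and stay still when incidence falls, because its denominator (measured fevers) arises after the intervention. All-cause fever is itself a listed outcome. Two analysts working from the Analytical plan could therefore compute different quantities for the primary outcome.

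**Working it through.** **1. The plan's own figure.** The 52 % cannot be reproduced, because the baseline clinical incidence is not stated. Working backwards with a two-proportion normal approximation, two-sided 5 % and 7914 split equally (all assumptions), 80 % power at a 52 % reduction implies a baseline risk of about 1.08 % per visit, or roughly 43 control and 20 intervention cases. With 7914 per arm it would be 0.54 %. Either way the unit is the person, not the test.

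**2. Notation.** Let m be malaria fevers and f other measured fevers per arm, and q0 = m/(m+f) the baseline positivity. Malaria fevers fall by r and other fevers by s. The document gives no q0, so 25 %, 50 % and 75 % are shown.

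**3. Weekly proportions, other fevers unchanged (s = 0).** The relative fall in positivity is 1 − (1−r)/(1 − r·q0). With r = 0.52:
- q0 = 0.25: 1 − 0.48/0.87 = 45 %
- q0 = 0.50: 1 − 0.48/0.74 = 35 %
- q0 = 0.75: 1 − 0.48/0.61 = 21 %

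With persons visited as denominator, the fall shows as 52 %.

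**4. Odds ratio of positivity.** This is (1−r)/(1−s).
- r = 0.52, s = 0: 0.48, so there is no bias.
- r = 0.52, s = 0.20: 0.48/0.80 = 0.60.
- r = s = 0.20: 1.00, so a real fall is invisible.
- r = 0, s = 0.20: 1/0.80 = 1.25, so the traps look harmful.

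The 20 % values are illustrations, not figures from the document.

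**5. Precision if a logit model used tests (s = 0).** Per person, with a rare outcome, the variance of the log effect is about 1/m0 + 1/m1. Per test it is 1/m0 + 1/m1 + 2/f. Set m0 = 1 and m1 = 0.48, so the first sum is 3.083, and f = (1−q0)/q0. Power is Φ[(0.84 + 1.96)/ratio − 1.96].

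| q0 | f | 2/f | SE ratio | Power |
|---|---|---|---|---|
| 0.25 | 3 | 0.667 | √(3.750/3.083) = 1.10 | 72 % |
| 0.50 | 1 | 2 | √(5.083/3.083) = 1.28 | 59 % |
| 0.75 | 1/3 | 6 | √(9.083/3.083) = 1.72 | 37 % |

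These figures cover sampling error only; the random effects for cluster and round are left out.

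**6. Cross-check.** Comparing positivity between arms directly, from the case numbers in step 1, gives power of about 73 %, 57 %, 41 % and 31 % at q0 = 0.2, 0.5, 0.7 and 0.8. This is a different approximation with the same pattern.

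**The case against.** The strongest reply is that the sentence describes a weekly tabulation. It includes counts as well as proportions, sits beside a parallel sentence on mosquito catches, and neither defines the outcome nor specifies the model. The objective, the surveillance of all individuals and the power section all point to persons. A binomial model can take one yes/no record per person-visit, and a condensed article may leave that detail to a fuller plan. This stands. A reader might infer that the primary outcome has been replaced by test positivity; the document does not say so.

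A reader might also infer that the model would understate a true effect. Step 4 shows otherwise for a logit model when other fevers are unchanged: the odds ratio stays at 0.48. The 45 %, 35 % and 21 % figures belong to the tabulated proportions.

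Finally, it is tempting to cite the Discussion's statement that "replacement of kerosene lamps by electric lights is likely to remove this health hazard" as evidence that the lights reduce other fevers. That statement concerns the respiratory system and never mentions fever. The secondary objective is also only partial support: all-cause fever includes malaria fever, so listing it does not show that other fevers will change.

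What remains is not mere silence. The plan states a proportion for incidence, and it is the wrong one for that outcome.

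**Conclusion.** The point holds in limited form. For the primary outcome, the only proportion written down is positivity among measured fevers, which conflicts with the incidence objective and the per-person power basis. The weekly series built on it would show a 52 % fall as 45 %, 35 % or 21 %, at the assumed baseline positivities.

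The consequences for the test are conditional on the model using tests, which the document leaves open. In that case power would be about 72 %, 59 % or 37 % instead of 80 % with other fevers unchanged, and the odds ratio would be biased if other fevers changed. All sizes rest on assumed positivity. The direction and amount of any change in other fevers are unknown.

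**What to change.** Split the sentence in the Analytical plan:

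- **Prevalence:** positive RDTs out of persons surveyed.
- **Clinical malaria:** persons with measured fever and a positive RDT out of all persons visited in that HDSS round, with untested persons counted as non-cases.

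State that the binomial mixed model for the primary outcome uses the same persons-visited denominator. Report RDT positivity among tested fevers as a separate descriptive series by arm.

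The cost is a few sentences and a re-tabulation. The Data entry and management section says the monitoring software tracks which individuals are visited. There is one small downside: the trial is unblinded and testing starts from self-reported fever, so a per-person rate is more exposed to differential fever reporting than positivity is. The separate positivity series and the already planned all-cause fever outcome help to check for that.

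### The weekly summary of the primary outcome divides by RDTs done, but HDSS RDTs are done only in currently febrile people, so the stated proportion is test positivity, not clinical malaria incidence

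*Protocol article*

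**What the plan says.** In the section on the main aim, the trial sets out to "measure the effect of mass mosquito trapping on clinical malaria incidence, measured as fever plus positive rapid diagnostic test (RDT) result".

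Under Measurement of malaria incidence and prevalence, "Clinical malaria incidence was recorded during the routine HDSS surveillance of all individuals", in three rounds a year. Two conditions stand between a visit and a test. The first is a report of recent fever: "If fever was reported to have occurred within 2 weeks of the visit, body temperature was measured". The second is a threshold on that reading ("If the measured in-ear temperature was greater than 37.4" °C). Only a resident who meets both is given a test. The separate prevalence survey tests every person selected.

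The Analytical plan names malaria fever incidence as the primary outcome. It then gives one sentence for both malaria outcomes: "the numbers and proportions of positive RDT tests were summarised by week and arm of the trial". The paragraph after that specifies binomial mixed models with a likelihood ratio test, without naming the binomial denominator or the link.

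The Power and sample size rationale takes as its basis "that of a single visit per person, occurring halfway through the rollout". It states 80% power for a reduction of about 52% in clinical incidence with an effective sample of 7914 persons.

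**The concern.** One summary is applied to two data sources with different testing rules. Where everyone is tested, positives divided by tests is a prevalence. Where only the currently febrile are tested, it is the share of tested fevers that are RDT-positive. A malaria fever that is prevented leaves both the numerator and the denominator, and a change in other fevers moves the ratio even when malaria does not change.

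The denominator is therefore something the intervention may itself affect. The protocol lists measured and reported all-cause fevers as a secondary objective. Its Discussion expects less exposure to kerosene fumes and possibly other health gains. The intervention is unblinded, and the first condition for testing is a self-reported fever.

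There is a second, smaller mismatch. A reported fever that has resolved by the visit is not tested, and visits take place three times a year. The count is of febrile malaria present at the visit, with no time at risk attached.

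What is at stake is the meaning of the main result: whether a reported percentage reduction refers to residents or to febrile people who were tested.

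**Working it through.** **1. The plan's own figure.** The stated power (80%, 52% reduction, 7914 persons) cannot be reproduced, because baseline incidence, significance level and sidedness are not given. It can be solved backwards with a two-proportion calculation, assuming α = 0.05, an equal split and no further clustering penalty:

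- 7914 in total: baseline 1.08% per visit two-sided, 0.85% one-sided.
- 7914 per arm: 0.54% two-sided, 0.43% one-sided.

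Rates this low fit persons seen as the unit. If the 7914 were tests at an assumed positivity of 23.7% (the protocol's RDT prevalence, borrowed for illustration), the detectable reduction would be about 11%, not 52%. Planning was therefore per person.

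**2. Positivity when RDT-negative fevers are unchanged.** Let t be baseline positivity and r the true reduction in RDT-positive fevers. New positivity = t(1−r) / [t(1−r) + 1−t]. The protocol gives no t, so a range is assumed. With r = 0.52:

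- t = 0.30: 0.144/0.844 = 0.171, a fall of 43%.
- t = 0.50: 0.240/0.740 = 0.324, a fall of 35%.
- t = 0.60: 0.288/0.688 = 0.419, a fall of 30%.

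**3. The same case on the odds scale.** Odds of positivity go from t/(1−t) to t(1−r)/(1−t). The odds ratio is 1−r = 0.48 for every t, so there is no dilution.

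**4. Precision.** Take the two-sided back-solved case with 3957 persons per arm. Expected positives are 3957 × 0.01077 = 42.6 against 42.6 × 0.48 = 20.5. At t = 0.30 the tests number 42.6/0.30 = 142 and 142 − 42.6 + 20.5 = 120. Comparing test proportions, power is:

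- persons as denominator: 80%
- tests, t = 0.30: 69%
- tests, t = 0.50: 57%
- tests, t = 0.70: 41%

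**5. If RDT-negative fevers also change.** Multiply them by q, with t = 0.50 and r = 0.52:

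- q = 0.80: 0.24/(0.24 + 0.40) = 0.375. Fall 25%, odds ratio 0.60.
- q = 0.48: 0.24/(0.24 + 0.24) = 0.500. No fall, odds ratio 1.0.
- q = 1.20: 0.24/(0.24 + 0.60) = 0.286. Fall 43%, odds ratio 0.40.

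The odds ratio equals (1−r)/q, so it overstates the effect whenever q exceeds 1. The proportion ratio equals (1−r) divided by the ratio of total tested fevers. It overstates the effect only if total tested fevers rise, that is, if q > 1 + tr/(1−t): 1.52 at t = 0.50, and 1.22 at t = 0.30.

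**6. q need not equal 1 even if non-malaria fever is stable.** Some non-malaria fevers test positive because of background parasitaemia. Suppose that background falls in step with transmission, from 23.7% to 11.4% (assumed), and that 30% of tested fevers are due to malaria. RDT-positive fevers go from 0.3 + 0.7 × 0.237 = 0.466 to 0.144 + 0.7 × 0.114 = 0.224, a ratio of 0.48. RDT-negative fevers rise from 0.534 to 0.620. The odds ratio of positivity is then 0.41.

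**The case against.** The strongest reply is that the quoted sentence describes a summary, not the inferential analysis. It covers both outcomes in one breath and speaks of numbers as well as proportions: proportions suit the prevalence survey, and numbers of positives are the natural numerator for incidence. The model paragraph names no denominator. The surveillance description and the power statement both point to persons, so the intended analysis may already be the one proposed here. The article is also a condensed account, and the exact model specification may sit in a fuller document.

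Much of this stands. The missing model denominator and link are not counted as a fault. A reader might infer that the primary test is run on test positivity and is therefore biased towards no effect. The document supports neither step. It does not say what the binomial model divides by. The dilution in step 2 exists only on the proportion scale; under a logit link with RDT-negative fevers unchanged there is none, and step 5 shows that the error can run either way.

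What does not fall away is the sentence itself. It names a denominator for incidence, tests, and no other denominator for that outcome appears in the Analytical plan. That is a stated quantity that disagrees with the objective and the power basis. Saying numbers as well does not repair it, because a weekly count by arm has no meaning as incidence until it is set against the residents seen in that week and arm, whose number changes as the rollout proceeds.

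**Conclusion.** The summary denominator for the primary outcome is wrong as written. For HDSS data, positives over tests is positivity among currently febrile people. It conflicts with the Primary objective and with the per-person, per-visit power statement.

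Whether the fault reaches the primary test cannot be told from the article. If it does, the size depends on scale and on other fevers. As a ratio of proportions, with RDT-negative fevers unchanged, a true 52% fall reads as 43%, 35% or 30% at assumed baseline positivity of 30%, 50% or 60%. As an odds ratio it stays at 0.48 with reduced power. If RDT-negative fevers change, neither measure is safe and no direction can be promised. A blanket statement that the effect is understated is not supported.

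These figures rest on baseline positivity that the document does not give. The power figures also assume α = 0.05 two-sided, an equal split, 7914 as the total and no clustering.

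The outcome is also better described as febrile malaria present at the visit than as incidence over time.

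**What to change.** For incidence, state that both the weekly summary and the binomial model use all residents seen at the HDSS visit as denominator, febrile or not. The event is a measured temperature above 37.4 °C together with a positive RDT. Keep the proportion of tests positive for the prevalence survey. For HDSS data, report it only as a secondary description, clearly labelled as test positivity.

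Describe the primary outcome as febrile malaria present at the visit. Say that its ratio is read as an incidence ratio only if fever duration is the same in intervened and non-intervened clusters.

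The cost is a few sentences. No new data are needed: the Data entry and management section says that the monitoring software tracks which individuals are visited each day. The downside is a small absolute rate (0.4% to 1.1% per visit in the back-solved cases) that cannot be called an annual incidence. In return, the primary result no longer divides by a quantity that shifts with non-malaria fevers, and it agrees with the basis on which the trial was powered.
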